### Outcomes

2.7.

A.NICU Phase

#### MRIs

2.7.1.

As above, we will aim for infants to undergo imaging every 2 weeks with at least 3 serial brain MRIs during the NICU phase: one at the time of enrollment in the study, and as soon as clinical condition allows; one or more interim scans at a frequency of approximately every 2 weeks; and a final scan at TEA in a 3 Tesla, off-unit scanner. We will use an automated segmentation technique (MANTiS) (33) to monitor the primary outcome i.e., evolution of total brain volumetrics as well as tissue-specific volumes of cortical grey matter, deep grey matter, white matter, hippocampus and cerebellum on sequential MRI scans of VP infants in the SENSE and reference groups. Secondary MRI outcomes will include fractional anisotropy in specific brain regions of interest which will be defined based on a validated method (34), and anticipated to include measures of white matter microstructure.

#### Maternal outcomes

2.7.2.

With parental consent, the study team will collect standard maternal demographic and pertinent perinatal course, along with infant clinical course data from the medical record. Demographic and family functioning measures will be collected from questionnaires given to parents at discharge. These will include: a general questionnaire regarding family composition and family-social risk factors, along with several standardized surveys to assess psychosocial and parenting experiences, including Hospital Anxiety and Depression Scale (39); Parental Stress Scale-NICU(40); and Parenting Sense of Competence Scale (41).

#### Infant outcomes

2.7.3.

As early neurobehavior is a good marker of outcomes at TEA (35), we will also obtain serial neurological assessments using the Premie-Neuro examination (36) around each MRI timepoint when possible. Around the time of the TEA brain MRI, an in-depth assessment of the infant's neurological status and neurobehavior will be conducted using the HNNE (37) and TIMP (38) standardized assessments. All neurological examinations will be performed by trained study staff and videorecorded for reliability and scoring purposes with parent consent. Examinations will be scored by an examiner blinded to infant group assignment.
B.Follow-up phaseAs part of the standard care at BWH, children born VP are routinely offered interdisciplinary specialty care in the BWH NICU follow-up clinic for serial neurodevelopmental surveillance and family counseling during early childhood. For the purpose of this study, the consent form will include permission to review the medical record and document the results of these evaluations. If any subjects do not qualify for clinical follow-up, we will offer families a separate research-only follow-up visit. The developmental follow-up is intended to occur serially, up to around age 2 years corrected for prematurity, with a final evaluation window between 22 and 26 months corrected age. The primary neurodevelopmental outcome will be assessed using the Bayley Scales for Infant and Toddler Development, 4th Edition (42) standardized instrument, in conjunction with a neurological examination around 2 years corrected age. Parental questionnaire data will also be sought to reassess the family's psychosocial and parenting experiences, along with child's developmental skills with standardized instruments routinely used during the 2 year follow-up clinical assessments including the Ages and Stages Questionnaire-3: 24 month parent questionnaire (43), The Modified Checklist for Autism in Toddlers (44), and The Pediatric Eating Assessment Tool (45).

To promote retention and mitigate loss to follow-up, we will employ multiple strategies to enhance family compliance with visits and continued engagement. These include ongoing contact with participating families by study coordinators in the NICU and following discharge, mailing birthday cards, and small incentives for study assessment completion at NICU stage as described in the approved IRB protocol. For families who do not qualify for, or choose not to return for clinical follow-up, we will offer a one-time research-only visit at 2-year corrected age.

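### The two-year Bayley-4 and neurological examination come by default from routine visits at the same hospital's follow-up clinic, and nothing stated keeps SENSE participation from the examiner

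*Protocol article*

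**What the plan says.** All of the following is in the protocol article.

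- **NICU phase (2.7.3, before the follow-up heading).** The Premie-Neuro, HNNE and TIMP are carried out by trained study staff and filmed if the parent consents. The masking rule follows: "Examinations will be scored by an examiner blinded to infant group assignment".
- **Follow-up phase, outcome (2.7.3, part B).** "The primary neurodevelopmental outcome will be assessed using the Bayley Scales for Infant and Toddler Development, 4th Edition", "in conjunction with a neurological examination around 2 years corrected age".
- **Follow-up phase, default source.** At this hospital "children born VP are routinely offered interdisciplinary specialty care in the BWH NICU follow-up clinic", which provides serial surveillance and family counseling. For the study, "the consent form will include permission to review the medical record and document the results of these evaluations".
- **Follow-up phase, fallback.** "If any subjects do not qualify for clinical follow-up, we will offer families a separate research-only follow-up visit". The retention paragraph widens this: "For families who do not qualify for, or choose not to return for clinical follow-up, we will offer a one-time research-only visit".
- **Use of the result (2.10).** Two-year Aim 3 outcomes are compared between exposure groups with an approach similar to that of the primary aim, including adjustment for baseline covariates.
- **Limitations (section 3).** These cover non-randomized allocation, selection and confounding, small size, exploratory status and possible group imbalance. Assessor knowledge of group is not among them.

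**The concern.** The article deals with masking for one phase and, for the other, fixes a data source without carrying the safeguard over. In the NICU phase, blinded scoring is workable because study staff perform the examination and a recording exists. At two years the default score is whatever the clinic recorded, and no recording or separate scoring is described for either type of visit.

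The Bayley-4 and a neurological examination depend on examiner judgement. Families know whether they joined SENSE, because exposure follows their own consent. The clinic belongs to the hospital that delivered the program, and it sees the child serially. If an examiner learns that a child had SENSE or SENSE-plus, expectation can move the score, and the error lines up with exposed versus reference. It arises at about 24 months, so adjustment for baseline characteristics cannot remove it. If awareness is not recorded at the visit, it cannot be examined afterwards. There are also two visit routes, and awareness may differ between them.

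**Working it through.** This is a design point, and the plan has no figure to correct. The only between-group power statement (2.8: at least 80% at d = 0.70, two-sided 5%) is for total brain volume on MRI at term-equivalent age. With 50 versus 25 infants it reproduces: 80.5% by the noncentral t. No power is stated for any two-year outcome, so d = 0.70 is not used as a yardstick here.

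**Does the masking rule reach the two-year visit?**

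| Feature | NICU-phase examinations | Two-year Bayley-4 and neurological examination |
|---|---|---|
| Performed by | Trained study staff | Follow-up clinic by default; research-only visit as fallback |
| Recording for scoring | Yes, with parent consent | Not stated |
| Scorer masked to group | Yes | Not stated for either route |
| Source of the data | Study examination | Medical record by default |

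The masking sentence precedes the follow-up heading and completes a description of filmed examinations by study staff. It does not cover the Bayley-4 on any reading.

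**Which contrast is exposed?**

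1. *Knowledge of brain injury.* Reference infants must also have a term-equivalent MRI (2.2, 2.3), and serial cranial ultrasound is routine in the unit for babies born before 32 weeks (2.6.1). Injury information is therefore available on both sides of exposed versus reference. The contrasts named in 2.10 within high-risk and low-risk infants share it more closely still.
2. *Knowledge of SENSE participation.* This differs between exposed and reference by definition, so it is the item that matters.

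**What would a shift do? (Illustration on assumed values only.)** Assume no true effect, 50 versus 25 children all followed up, independent observations, and a uniform shift of b SD in exposed children's scores. The noncentrality is b / √(1/50 + 1/25) = b / √0.06 = b / 0.245, with 73 degrees of freedom and a two-sided 5% critical value of about 1.99.

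| Assumed shift b (SD) | Noncentrality | Chance of a significant result |
|---|---|---|
| 0 | 0 | 5.0% |
| 0.1 | 0.41 | 6.9% |
| 0.2 | 0.82 | 12.7% |
| 0.3 | 1.22 | 22.7% |

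The documents support no particular value of b, including zero. The table shows only that a small systematic shift is not negligible at this sample size.

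**The case against.** **Silence is not a statement.** A reader might infer that the two-year examiners are unmasked. The article does not say so. It is a condensed account that refers to an IRB protocol not shown here, where visit arrangements may be set out. This stands as a limit on the claim. The point survives because the article does set a masking rule, places it in one phase, and fixes a source for the other phase that does not carry it.

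**What clinic staff know is inferred.** A reader might infer that SENSE participation sits in the clinical chart. The article places the bedside-log data in a research database (2.4.1) and study data on secure research systems (2.5). It does not say that group enters the chart. This also stands. Families remain a route to the examiner, and nothing stated closes it.

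**Injury findings as the source of bias.** A reader might extend the concern to examiners who know the MRI results, or to high-risk versus low-risk children. Injury information is available in the reference group too, and the risk groups differ in actual injury by design. That extension is not supported.

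**The word 'all'.** The sentence on neurological examinations could be stretched to the two-year neurological examination. Its position and its reference to study staff argue against that, and the Bayley-4 would still be uncovered.

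**Stakes.** A reader might take 'primary' to mean the study's primary outcome. That is brain volume by automated segmentation (2.7.1), which this point does not touch. Aim 3 is secondary and exploratory, and the authors call observed associations preliminary. This lowers the priority, but it does not remove a bias that would run in one direction.

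**Conclusion.** The point holds as a gap in a stated design. The primary neurodevelopmental outcome of the follow-up phase is examiner-scored and comes by default from routine clinic evaluations. No stated step keeps SENSE participation from the examiner at either a clinic or a research-only visit. The concern is mainly the exposed-versus-reference contrast.

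The size of any bias cannot be estimated from the document, and the direction is not established either. The conclusion rests on two assumptions: that Bayley-4 and neurological scores respond to examiner expectation, and that some examiners will learn of participation. The second is plausible because families know their exposure, but it is not documented. The matter is worth correcting before two-year visits accumulate, because awareness that was not recorded cannot be recovered. It is not a threat to the study's main result.

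**What to change.** 1. Extend the masking rule in 2.7.3 to SENSE group at the two-year visit, on both routes. Keep SENSE participation out of the visit referral and the pre-test summary, and ask families not to mention it before testing. Clinicians' access to imaging and the rest of the chart stays as it is.
2. Record for each assessment whether the examiner knew the child's group, and whether the visit was clinic or research-only.
3. Repeat the two-year exposed-versus-reference comparison in masked assessments only, as a sensitivity analysis.
4. Where masking is not possible, say so and add it to the limitations in section 3.

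**Cost.** One visit instruction, a request to families, two data fields and one extra analysis, with no new staff. Masking will be incomplete for clinicians who already know the child, and the recorded field will show how often. The masked-only subset will be small, drawn from at most 75 children before loss to follow-up. It can show whether the estimate moves, but it will not settle the question.

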### Sample size

2.8.

For the primary aim, the proposed study has ≥80% power to detect differences in brain growth (total brain volume) on MRI at TEA between the SENSE (low- and high-risk groups combined) and reference groups of moderate to large effect sizes (Cohen's *d* = 0.70) using a two-tailed test with α=0.05. The power of the proposed study is sufficient to detect effect sizes reported in studies including a trial of early sensitivity training in parents of preterm infants (*n* = 45) which reported large effect sizes of *d* = 0.75–1.10 in white matter maturation and connectivity by ADC and FA between groups (46). The proposed study is further powered to detect small to moderate effect sizes (*d* = 0.41) between repeated brain measurements and moderate effect sizes (*d* = 0.59) in each SENSE subgroup individually (SENSE or SENSE-plus, *n* = 25 each) (Aim 2). Brain growth measured as total tissue, unmyelinated white matter, and cortical gray matter have been previously reported to exhibit moderate to very large effect sizes (*d* = 0.72–2.41) when comparing measures before and after 33–34 weeks gestational age (17).

### Adverse events

2.9.

Serious adverse events or study complications in this cohort study are not anticipated, as risks to subjects are minimal. Safety concerns will be addressed immediately with the principal investigator. The principal investigator will attend regular meetings with the study team where any safety issues are further discussed and then presented to the Institutional Review Board (IRB) if required. Severe or urgent safety concerns will be communicated immediately to the principal investigator who will report immediately to the IRB. Adverse events temporally related to participation in the study will be documented whether or not they are considered related to the test article.

### Data analysis

2.10.

Descriptive statistics of key demographic and clinical characteristics will be reported overall and by group status (exposed vs. reference) using means and standard deviations (or medians and interquartile ranges, as appropriate) for continuous and number and percentage for categorical variables. Differences by group status will be tested using chi square (or Fisher's exact test where cells <5) and Wilcoxon rank sum or Kruskal-Wallis tests, as appropriate, for categorical and continuous variables, respectively. Similar statistics will be reported by risk status among exposed infants including fidelity of implementation of the SENSE or SENSE-plus program in the low-risk and high-risk groups (>75%, 50%–75%, 25%–50%, and <25% compliance with total amount of recommended sensory exposure in each category). For the primary aim, outcome among infants in the SENSE program (exposed group) will be compared with the unexposed, similarly eligible infants whose families did not enroll in the neuropromotive program. Differences in outcome by group status will be analyzed using linear mixed models [or multinominal regression using generalized estimating equations (GEE) for ordinal categories of injury] to adjust for intrafamilial correlation among multiple births in models unadjusted and adjusted for potential bias (selection and confounding) by baseline covariates associated with both SENSE status and outcome. The study will also examine the difference between groups by exposure and high/low risk status, i.e., high risk: exposed vs. unexposed and low risk: exposed vs. unexposed. To address small sample size, we will utilize robust estimation methods. We will use a similar approach to assess differences between exposure groups for Aim 3 outcomes assessed at NICU discharge and at age two corrected age. Analysis of the change in repeated measures (Aim 2, SENSE groups only) will be modeled using linear mixed models and GEE, as appropriate, with fixed effects for SENSE group status, time, and the interaction between group and time. For assessment of change between two assessment time points, models will include fixed effects for group status and baseline assessment. We will use a similar approach to model Premie-Neuro exam scores (Aim 3) assessed at each serial MRI measurement for exposed infants. Analyses are exploratory and thus multiple comparisons will not be adjusted. Statistical analyses will be run using SAS v9.4 software (SAS Institute Inc., Cary, NC, USA) and IBM SPSS version 24.0 (IBM Corp, Armonk, New York, USA).

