### Design

2.2.

This is a prospective cohort study of VP infants born at or before 32 weeks gestation in an academic, 66-bed level III NICU at Brigham and Women's Hospital in Boston, MA. The study will aim to enroll a total of 75 born consecutively infants divided in three study groups. Exposed infants will be categorized into two exposure groups (group 1: low-risk or group 2: high-risk) based on the degree of neurological injury on early brain magnetic resonance imaging (MRI) at enrollment, with 25 infants intended to enroll in each exposure group. Exposed infants in group 1 (low-risk, *n* = 25) will receive protocolized neurodevelopmental support utilizing the SENSE program. Exposed infants in group 2 (high-risk, *n* = 25) will receive the SENSE program in addition to enhanced neurorehabilitative support (SENSE-plus). The enhanced neurorehabilitation support will extend beyond the NICU standard of developmental care to include additional targeted visits that will consist of skilled neonatal developmental therapy sessions 4–5 times per week. The dose and frequency of sensory exposures in the groups receiving the SENSE program are anticipated to be delivered primarily by the infant's family, with education and support from NICU staff. Sensory experiences and neuropromotive interventions will also be tracked in both groups. Infants in the SENSE program will be compared with group 3 consisting of *n* = 25 reference (unexposed) infants whose families did not wish to enroll in the neuropromotive program, have undergone a term-equivalent brain MRI for clinical or other research purposes, and their parents subsequently provide informed consent to enrolling in the reference/unexposed group. Enrollment in each of the three groups will occur continuously until total sample size for each group is achieved.

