Developmentally sensitive bedside care OT or PT/Motor therapy: • 8–34 weeks PMA: total of 1–3 sessions per week • >34 weeks PMA: total of 2–4 sessions per week If known neurological injury or neurologic exam differences, or parent education and support need: consider increasing therapy to 2–4 times/week Neurologic assessments: • Brain MRI at TEA if <28 weeks GA at birth, or >28 weeks GA and additional risk factors per NICU guideline • TIMP at TEA by PT/OT in NICU • TIMP at 3–4 months PMA by OT in outpatient follow-up clinic SLP/Feeding therapy: • 33–34 weeks PMA: 1–2 times/week • >34 weeks PMA: 2–4 times/week Feeding assessment: • Assessment of feeding skills progression with FOIS-P (31) feeding scale	Neonatal therapy and assessment per reference Group, plus the following: • SENSE Program delivery with weekly targets for sensory experiences from enrollment to TEA • Therapist-guided parent training on reading infant's behavioral cues and contingent responses • Therapist-led education on positive auditory experiences (facilitating reading, music exposures per SENSE goals for GA) Neurologic assessments: • Brain MRI every 2 weeks from enrollment until TEA • Premie-Neuro every 2 weeks with MRI • TIMP and HNNE at TEA by PT/OT and research nurse • TIMP at 3–4 months PMA by OT in outpatient follow-up clinic Feeding assessment: • Assessment of feeding skills progression with FOIS-P (31) feeding scale	Neonatal therapy and assessment per Low-Risk Group, plus the following: Enhanced therapy involvement based on serial assessments and imaging results, as follows: • Additional 1–2 skilled OT or PT weekly sessions (totaling service delivery to 4–5 days/week) • Motor therapy goals targeted based on results of formal neurologic assessments, focus on areas requiring further therapist-guided interventions (e.g. postural control, midline orientation, symmetrical movements, motor experience) • OT/PT increased availability to facilitate day-shift routine care times with staff/parents (i.e. facilitation diaper changes, handling time) • Increased reading with infant several times a week (optimal: daily) • Enhanced family education with parent instructional videos

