#### Timeline of MRI scans

2.6.1.

In our NICU, the clinical standard of care entails that babies born extremely preterm (before 28 weeks gestation), or VP (28–32 weeks gestation) with additional risk factors such as moderate-severe bronchopulmonary dysplasia, stage II or higher necrotizing enterocolitis, need for major surgery, severe growth restriction, or documented neurological abnormality on CUS among others, are considered for a TEA brain MRI. The TEA scan typically occurs between 38 and 42 weeks PMA or within the week of discharge, whichever comes first. Infants typically undergo brain MRI scanning without sedation in the study unit (20), using the documented “feed and wrap” method (32) (Figure 2). Serial CUS imaging is also obtained routinely in our unit for babies born before 32 weeks gestation per a clinical practice guideline, typically on days of life 1, 3, 7, 30, and 60. However, with only scarce evidence-based understanding of the etiology of many neuronal disorders available, findings on both serial CUS and TEA MRIs leave many unanswered questions in terms of etiology, timing, and evolution of injury prior to TEA, which have implications for the child's developmental trajectory and therapy needs post NICU discharge.

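### Reference infants enter only through a term-equivalent MRI done for another reason, a selection step that SENSE infants do not face and that the planned adjustment may not remove

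*Protocol article*

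**What the plan says.** **The comparison.** The Data analysis section states that outcome in the SENSE program "will be compared with the unexposed, similarly eligible infants whose families did not enroll in the neuropromotive program". Models are run unadjusted and adjusted for baseline covariates associated with both SENSE status and outcome. Exposed-versus-unexposed contrasts within high-risk and within low-risk infants are also planned. The Sample size section claims "≥80% power to detect differences in brain growth (total brain volume) on MRI at TEA" for the contrast "between the SENSE (low- and high-risk groups combined) and reference groups".

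**How each group reaches the TEA scan.** Under Timeline of MRI scans, low-risk and high-risk SENSE infants undergo a study MRI at TEA. Under Informed consent, Design and Study subjects, reference infants meet the inclusion criteria, are not in SENSE, and have a TEA MRI for a clinical or other-research reason. The Design section adds that "their parents subsequently provide informed consent to enrolling in the reference/unexposed group".

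**Who gets a clinical TEA scan.** The reference column of Table 1 gives "Brain MRI at TEA if <28 weeks GA at birth, or >28 weeks GA and additional risk factors per NICU guideline". Timeline of MRI scans says infants born before 28 weeks are considered for a scan, as are those born at 28–32 weeks "with additional risk factors such as moderate-severe bronchopulmonary dysplasia, stage II or higher necrotizing enterocolitis, need for major surgery". It also lists severe growth restriction and an abnormal cranial ultrasound (CUS), and leaves the list open.

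**What is acknowledged.** The limitations in the Discussion cover differences between families who do and do not consent. They do not mention selection through the reason for the MRI.

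**The concern.** The outcome is total brain volume at TEA. Entry to the reference group depends on having that scan, and on the clinical route the scan depends on immaturity and morbidity. The Introduction itself says that such morbidities affect brain growth. An uncomplicated infant born at 28–32 weeks can enter SENSE, but has no evident clinical route into the reference group.

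Birth gestation, growth restriction and early CUS findings can be known by enrolment and so can be adjusted for. Bronchopulmonary dysplasia, necrotizing enterocolitis and surgery can arise after SENSE enrolment, which is intended by 32 weeks postmenstrual age, so they need not be baseline covariates. If few uncomplicated 28–32-week reference infants exist, adjustment also has to extrapolate. The low-risk exposed-versus-unexposed contrast would be hit hardest.

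Two further features add to this. SENSE is fixed at 25 low-risk and 25 high-risk infants, whereas the reference group has no injury quota. Reference consent follows the scan, when its result may be known. At stake is whether a volume difference in the powered contrast can be read as related to SENSE rather than to who was scanned.

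**Working it through.** **1. The plan's own figure.** Inputs from Sample size and Design: 50 SENSE (25 + 25) against 25 reference; effect "of moderate to large effect sizes (Cohen's *d* = 0.70"; "using a two-tailed test with α=0.05".
- Standard error in SD units: √(1/50 + 1/25) = 0.245.
- Noncentrality: 0.70 / 0.245 = 2.86 on 73 degrees of freedom.
- Power: 0.805 by noncentral t (0.815 by normal approximation).

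The stated power of at least 80% is reproduced. It takes any mean difference between groups to be the effect of interest.

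**2. Entry conditions side by side.**

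| Condition | SENSE | Reference |
|---|---|---|
| Inclusion criteria (born at or before 32 weeks, etc.) | yes | yes |
| Source of TEA MRI | study protocol | clinical or other research |
| Clinical scan tied to birth <28 weeks or added risk factors | not needed | yes, on the clinical route |
| Share with early injury | 25/50 = 50% by quota | not fixed |
| Consent relative to TEA scan | before | after |

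**3. Size of the MRI-indication component.** The documents give no inputs, so these are assumptions. Let p_R and p_S be the shares of reference and SENSE infants meeting the unit's TEA-MRI criteria, and δ the volume deficit, in SD, of infants who meet them. Then the unadjusted bias = (p_R − p_S) × δ, positive in favour of SENSE. Rejection is that of a two-sided 5% t-test, 50 against 25, with no true effect.

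With p_R = 1:

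| p_S | δ | Bias (SD) | Share of 0.70 | Rejection |
|---|---|---|---|---|
| 0.8 | 0.5 | 0.10 | 14% | 7% |
| 0.8 | 1.0 | 0.20 | 29% | 13% |
| 0.5 | 0.5 | 0.25 | 36% | 17% |
| 0.5 | 1.0 | 0.50 | 71% | 52% |

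**4. Allowing for research scans.** These lower p_R; their share is not stated.
- p_R = 0.8: bias from (0.8 − 0.8) × δ = 0 to (0.8 − 0.5) × 1.0 = 0.30 SD; rejection 5% to 23%.
- p_R = 0.6: bias from (0.6 − 0.8) × 1.0 = −0.20 to (0.6 − 0.5) × 1.0 = +0.10 SD, so the sign can reverse.

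**5. A second set of assumptions.** With p_R − p_S of 0.2 to 0.6 and δ of 0.3 to 0.8 SD, the bias is 0.2 × 0.3 = 0.06 to 0.6 × 0.8 = 0.48 SD, and rejection is about 6% to 49%.

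**6. The injury quota.** If a share q of reference infants have early injury with deficit δ_inj, this component is −(0.5 − q) × δ_inj, which works against SENSE whenever q is below 0.5. It overlaps with step 3, because a CUS abnormality is itself an MRI trigger. With q unknown, the net bias cannot be signed.

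**7. Precision of restricted sets.** The effect detectable with 80% power is d = 0.70 for 50 against 25, 0.75 for 35 against 25, and 0.80 for 35 against 20. The 35 and 20 are assumed counts.

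**The case against.** The strongest reply has five parts.

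- **Eligibility wording.** Reference infants do meet the inclusion criteria, so calling them similarly eligible is literally correct, and the same section goes on to adjust for selection and confounding. This stands: the phrase does not claim exchangeability.
- **The clinical route is neither closed nor the only one.** Infants *are considered* for a scan, the risk list is open, and research scans also qualify. This stands, and it means a reader should not infer that every reference infant is extremely preterm or seriously ill.
- **Injury is partly handled.** The planned high-risk and low-risk contrasts address the injury mix, and several MRI triggers can be measured by enrolment. This stands in part. The powered contrast pools both SENSE groups, and later morbidity remains out of reach of baseline covariates.
- **The rejection rates come from an unadjusted test of one bias component.** This stands. They are not the error rate of the planned adjusted model.
- **The study calls itself exploratory and its findings preliminary.** That lowers the stakes, but the protocol still states power for exactly this comparison, and exploratory estimates can still be biased.

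The exact covariate list may properly sit in an analysis plan that is not shown. Its absence is not part of this point. The reference entry rule is fixed in the protocol itself.

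**Conclusion.** The point holds in a bounded form. Reference entry carries a condition linked, on the clinical route, to gestational age and morbidity, and SENSE entry does not. The two groups are alike on inclusion criteria only. Baseline adjustment may not remove the difference, and the limitations do not name it.

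The size is not determined by the documents. The 0.10–0.50 SD and 7–52% range is an illustration that assumes every reference infant meets the unit's criteria, 50–80% of SENSE infants do, the deficit is 0.5–1.0 SD, and no adjustment is made. It shrinks if many reference scans are for research.

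A reader might infer that the comparison is biased in favour of SENSE, or that the trial's false-positive rate is as high as 52%. The documents support neither. The injury quota can pull the other way, the research share is unknown, and the planned model adjusts for part of the imbalance. Nor do they show that scan results influenced reference consent, only that the sequence allows it.

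**What to change.** Keep the all-infant comparison as primary, and make these changes:

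1. Record for every infant in all three groups the reason for the TEA MRI and whether the unit's TEA-MRI criteria were met.
2. Put gestational age at birth and early injury stratum in the primary adjusted model.
3. Prespecify two key sensitivity analyses: one restricted to infants born before 28 weeks, where the indication is fixed at birth, and one restricted to infants meeting the criteria. State that the second conditions on morbidity that can arise after enrolment, which is why it should not replace the primary analysis.
4. Seek the records-only reference consent when SENSE is declined, before the TEA scan.
5. Qualify similarly eligible as referring to the inclusion criteria, and name MRI-indication selection among the limitations.

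The cost is small data collection (the criteria field can be derived from the chart), revised analysis wording, and an ethics amendment for consent timing. The restricted sets lose precision: if 35 SENSE infants qualify, the detectable d is about 0.75 against 25 reference infants and 0.80 against 20. The <28-week set may be smaller still; its size cannot be read from the protocol.
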